**Title**

Safety and efficacy of single-dose and triple-dose albendazole and mebendazole against soil-transmitted helminth infections in humans: open-label randomized-controlled trial in China

**Introduction**

The Memorandum of Understanding (MoU) formalizing the research collaboration between the Swiss Tropical Institute (STI) in Basel and the National Institute of Parasitic Diseases (IPD) in Shanghai has been renewed in early 2008. Within this frame, a close research partnership between the research groups of [name]. [name] at IPD and [name]. [name] at STI has been established. Supervised by [name]. [name], [name] completed a Ph.D. in Epidemiology in November 2007. On 1 September 2008, [name] started his 2-year post-doctoral studies at IPD, jointly financed by the Swiss National Science Foundation (SNSF) and IPD.

The proposed randomized-controlled single-blind trial will establish the safety and efficacy of single- and triple doses of the standard anthelminthic drugs albendazole and mebendazole for the treatment of common soil-transmitted helminth (STH) infections in humans. Globally, STHs infect more than one billion people and combined, the burden due to these worms might be approaching that due to malaria. In China, these parasites are still common, especially in southern and western areas of the country where the socio-economic development and available sanitary infrastructure lack behind the standards achieved in the eastern parts of the country.

The proposed study will be implemented in southwest China in Nongyang village, Menghai county, Xishuangbanna prefecture, Yunnan province. The investigators have already worked in this village in 2006, and a randomized-controlled trial comparing single-dose albendazole with single-dose tribendimidine had been performed in a neighboring village in 2007 (EKBB No. 149/07) (Steinmann et al., 2008b). Thus, the team is well acquainted with the local conditions, and has established a close network of local contacts.

**Background**

Soil-transmitted helminths (STHs), namely *A. lumbricoides*, *T. trichiura* and the hookworms (*Ancylostoma duodenale* and *Necator americanus*), are pervasive in poor rural and deprived urban settings in tropical and subtropical environments (Bethony et al., 2006). Each of these worm species infects hundreds of millions of people, and many hosts harbor multiple species concurrently. STHs belong to the so-called neglected tropical diseases (NTDs). Whilst mortality attributable to STHs is low, these parasites are responsible for chronic and inconspicuous morbidity that has been largely underappreciated. Indeed, new research suggests that STH infections and, in an exacerbated way, multiparasitism result in significant morbidities and disabilities (Ezeamama et al., 2005b). Effects include iron-deficiency anemia, negative birth outcomes, malnutrition, and impaired physical and cognitive development (Ezeamama et al., 2005a). There is a paucity of high-quality data on the burden caused by STHs but the combined burden of disease (BoD) due to STH infections might be similar to that owing to malaria. Affected individuals cannot realize their full biological and intellectual potential. As a result, the economic perspectives of already disadvantaged societies are diminished, and the vicious cycle of poverty and disease sustained (Hotez et al., 2006).

Global STH control efforts currently rely on repeated mass drug administration (MDA) of single-dose anthelminthics targeting school-aged children or entire communities, depending on the estimated local prevalence (WHO, 2006). MDA is usually done without prior individual diagnosis. Only four drugs are included in the World Health Organization’s (WHO) Model List of Essential Medicines to treat human STHs, and global STH control currently relies on two of them, i.e the benzimidazoles albendazole and mebendazole (Keiser and Utzinger, 2008). Both drugs are marketed for decades already and have been extensively used worldwide. Yet, few systematic and standardized studies comparing their efficacy have been published, and reported values vary widely. However, evidence from a recent meta-analysis of published randomized, placebo-controlled drug efficacy studies indicates a marked superiority of albendazole, most notably with regard to curing hookworm infections. It was also found that previous studies are often hampered by the lack of a diagnostic ‘gold’ standard and poor study design issues (Keiser and Utzinger, 2008). Standard single-dose oral regimens usually result in high egg-count reduction rates for the common STHs, but cure rates can be low, particularly for hookworm and *T. trichiura*. Still, it is routinely assumed that albendazole and mebendazole can be used interchangeably, and currently more often than not the choice of the anthelminthic drug is based on availability, cost and policy rather than sound evidence.

China has fallen back behind other countries in the Western Pacific region regarding the control of common STHs. A national STH control programme has been established but regular MDA to vulnerable groups (pre-school and school-aged children, women of childbearing age) has not been achieved, not to mention a MDA programme covering the whole population at risk (Albonico et al., 2008).

The results of the proposed study will lead to a better understanding of the safety and efficacy of today’s standard anthelminthic treatment. The data will provide evidence to STH control programme managers regarding drug and dosage selection, and will inform the Chinese national helminth control programme regarding the drug-dosage combination of choice. Moreover, the data will directly benefit the local population since the results will be used in an upcoming evaluation of integrated intestinal helminth control tools investigating the additional benefit of health education and provision of improved sanitation over the effect of the most efficacious drug.

**Study aim and hypotheses**

*Aims:*

To assess the safety and efficacy of single-dose and triple-dose oral albendazole and mebendazole against common soil-transmitted helminth infections (i.e. *Ascaris lumbricoides*, hookworm and *Trichuris trichiura*) in a highly endemic setting in China, and to use this evidence-base to guide mass drug administration programs.

*Hypotheses:*

1. Both albendazole and mebendazole are safe for treating common soil-transmitted helminth infections in humans.
2. Single-dose oral albendazole and single-dose oral mebendazole are both highly active against *A. lumbricoides*, and result in high fecal egg count reduction rates for hookworm and *T. trichiura*.
3. Single-dose oral albendazole is more efficacious than single-dose oral mebendazole against hookworm infections.
4. Triple-dose oral albendazole and triple-dose oral mebendazole are significantly more efficacious against *T. trichiura* than single-dose oral regimens.

**Study design**

*Study type*

Open-label (single-blind) randomized-controlled trial with four arms:

1. Single-dose albendazole
2. Single-dose mebendazole
3. Triple-dose albendazole
4. Triple-dose mebendazole

*Primary outcome*

Cure rates of single-dose and triple-dose oral albendazole and mebendazole for treating common STH infections, especially hookworms.

*Secondary outcomes*

1. Safety of single-dose and triple-dose oral albendazole and mebendazole against common STH infections.
2. Egg-reduction rates of single-dose and triple-dose oral albendazole and mebendazole against common STH infections.

*Instruments*

Repeated quantitative fecal egg counts by the standard Kato-Katz thick smear method (Katz et al., 1972) and the recently developed, arguably more sensitive FLOTAC method (Cringoli, 2006; Utzinger et al., 2008).

Severity-graded assessment of treatment-related adverse effects using a questionnaire.

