The total number of available diagnostic results will thus be: two Kato-Katz thick smears/sample, one FLOTAC apparatus with two different solutions/sample (total: three diagnostic test results/sample; six diagnostic test results at baseline). Kato-Katz thick smear slides and the FLOTAC are both read quantitatively.

*Randomization and drug dosage*

All participants with complete diagnostic results will be listed in ascending order according to their identification number, and the four different treatment options coded 1-4. A random sequence of 1s, 2s, 3s and 4s will then be generated, and aligned with the list of participants, thus assigning each individual a specific drug-dosage combination.

The drug dosage will be:

Daily albendazole dose: 400 mg (1 day or 3 days)

Daily mebendazole dose: 500 mg (1 day or 3 days)

For each participant, an identical envelope labeled with his/her name and containing the appropriate drugs according to the assigned treatment will be prepared.

*Treatment procedures, drug dosage and application*

Upon completion of the baseline parasitological survey, all participants with complete diagnostic results and ≥1 STH infection will be invited for treatment. They will be informed again about the treatment procedures, asked not to drink alcohol on treatment days, and to disclose their health and pregnancy status prior to treatment. On the days of treatment, teams of local health personnel and study team members will visit the participants individually in their houses after dinner time, enquire about their health and pregnancy status, and distribute the allocated drugs together with bottled water. Drug intake will be directly observed. This procedure will be repeated two times for those participants allocated to triple-dose treatment.

*Safety assessment:* All participants will be interviewed regarding adverse events of the treatment 24 h after drug application using a detailed semi-quantitative questionnaire providing a grading system for reported symptoms (Appendix 3). A medical doctor will be permanently available to the participants for 24 h after drug application for immediate attention to any adverse drug-related events which will be described in detail on an individual basis.

*Sample collection and diagnostic procedures for follow-up parasitological survey*

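### Safety collection is worded as treatment-related events, which permits a record filtered by attribution in a trial where the number of doses is visible

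*Protocol*

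**What the plan says.** Safety is the first secondary outcome in the protocol's Study design section: "Safety of single-dose and triple-dose oral albendazole and mebendazole against common STH infections". The first hypothesis under Study aim and hypotheses is that "Both albendazole and mebendazole are safe for treating common soil-transmitted helminth infections in humans".

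Three places describe how safety data are collected:

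- Study design, Instruments: "Severity-graded assessment of treatment-related adverse effects using a questionnaire".
- Treatment and study procedures, Safety assessment, on the interview: "All participants will be interviewed regarding adverse events of the treatment 24 h after drug application using a detailed semi-quantitative questionnaire". The sentence continues with "providing a grading system for reported symptoms (Appendix 3", so what is graded is the symptoms that participants report.
- The same paragraph, on the doctor available after dosing: "immediate attention to any adverse drug-related events which will be described in detail on an individual basis".

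The design is labelled "Open-label (single-blind) randomized-controlled trial with four arms". The title uses only the open-label term, the Introduction and the ethics section use single-blind, and no section says who is blinded. Envelopes are identical in appearance, but two further home visits with observed intake take place in the triple-dose arms only. The content of the Appendix 3 form is not shown.

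**The concern.** Each description ties the events to the treatment, and none commits to recording events regardless of cause. No criteria for relatedness are given, and nobody is named to judge it. A field team following this wording could reasonably leave out a symptom that the participant or interviewer put down to something else.

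The effects the protocol expects (nausea, vomiting and other short-lived gut complaints, under Risk/benefit assessment) are non-specific, so their cause is a matter of judgement. That judgement would be made by people who know how many doses were given. A participant treated on three evenings may blame the drug more readily, or less readily, than one treated once.

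All four arms receive active treatment, so the randomised contrast between arms is the main internal control for safety. The Background says the results should guide the choice of drug and dose, so readers will naturally look at single- against triple-dose safety. An event left off the form cannot be recovered at analysis, which makes this a data-collection matter and not one to leave to an analysis plan.

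**Working it through.** **The plan's own figure.** The protocol gives no event rate or calculation for safety. Its only calculated sample size is 44 per arm for hookworm cure (75% against 45%, one-sided α 0.05, 90% power). The pooled-variance formula for two proportions without continuity correction returns 44 per arm, with power 90.1%, and 4 × 44 = 176 as stated. No safety quantity enters it, so it is untouched by this point.

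**The wording, side by side.**

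1. Instruments limits the questionnaire to treatment-related effects.
2. The interview asks about events of the treatment. This can mean events caused by treatment or events following it.
3. The same sentence says that reported symptoms are graded, which points to a broader record. However, those symptoms are reported in answer to a question framed around the treatment.
4. The doctor's detailed description covers drug-related events.
5. No causality scale, attribution step or rule for discarding symptoms is described, and there is no statement that all events are kept.

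The text therefore permits a related-only record without clearly requiring one.

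**Who knows what.** The extra visits reveal the number of doses to participants and visiting teams under either blinding label. With identical envelopes and an unresolved label, knowledge of the drug itself is not established.

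**Illustration (all inputs assumed).** Let *s* be the true symptom rate, equal in both arms, and *a* the share of symptoms attributed to treatment. The recorded rate is *s* × *a*.

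- *s* = 0.20, *a* = 0.40 (single) and 0.70 (triple): 0.20 × 0.40 = 0.08 and 0.20 × 0.70 = 0.14. The spurious difference is 6 points.
- *s* = 0.20, *a* = 0.50 and 0.60: 0.10 and 0.12, a difference of 2 points.
- Equal *a*: difference 0.

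The apparent risk ratio is the ratio of the two *a* values and does not depend on *s*. With 50% in one arm and 50%, 70% or 90% in the other, it is 1.0, 1.4 or 1.8. The level also falls: with *a* = 0.40, a true 20% is recorded as 8%.

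**Against sampling error.** For 8% and 14% with 44 per arm, the standard error of the difference is √[(0.08 × 0.92 + 0.14 × 0.86)/44] = √(0.194/44) = 0.066, or 6.6 points. Pooling the two single-dose and the two triple-dose arms (88 each) gives √(0.194/88) = 0.047, or 4.7 points.

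**The case against.** The strongest reply is that no filter is actually described. All participants are interviewed, reported symptoms are graded, and treatment-related may be loose language for events after treatment. The title of Appendix 3 speaks of adverse events without a relatedness qualifier, and the form may already list every symptom. The doctor's description may only add narrative detail without limiting the questionnaire. This stands to the extent that use of relatedness as a filter is not established. It does not remove the ambiguity in the body text.

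A reader might also infer several stronger things that the documents do not support:

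- That unrelated events are never recorded. No discard step is stated, and the form is not shown.
- That those judging relatedness know the drug. Only knowledge of the number of doses follows from the text.
- That every between-arm safety comparison is biased. The Data analysis section names no safety comparison, the safety hypothesis is stated per drug, and a visible number of doses does not by itself distort albendazole against mebendazole at the same number of doses.

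It is also fair to say that the largest difference illustrated is smaller than one standard error for two single arms of 44. Unlike sampling error, though, such a bias does not shrink as numbers grow. Finally, people who know how many doses they received may report symptoms differently whatever the form asks, so broader recording would not make the single- versus triple-dose contrast free of bias.

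**Conclusion.** The point holds as a defect of wording and measurement for a secondary outcome. As written, the protocol permits a safety record limited to events judged related, without criteria or an assessor, in a trial where the number of doses is visible. Bias in the single- versus triple-dose contrast needs two further conditions: that relatedness is used as a filter, and that attribution differs by number of doses. Understated rates for the hypothesis that the drugs are safe need only the first, provided that some true effects are judged unrelated. Neither condition can be confirmed from the documents, and no size can be derived from them. The 0 to 6 points and the risk ratios of 1.0 to 1.8 are illustrations under assumed inputs. The cure-rate outcome and the sample size are unaffected. The change is worth making because it is cheap and the loss, if it occurs, cannot be repaired later.

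**What to change.** Reword Instruments (Study design) and Safety assessment (Treatment and study procedures) to say that every symptom or event reported in the post-dose window is recorded and graded whatever its suspected cause. Use all recorded events for the arm summaries and for any comparison between arms. Record suspected relation to treatment as a separate item, report it as secondary, and state who makes that judgement. Align Appendix 3 if it does not already work this way; if it does, only the body text needs to change.

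The cost is a wording change, one more column on the form and somewhat higher reported event rates. The change removes the attribution filter. It does not remove reporting bias from participants knowing their number of doses, and the report should say so.

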**Inclusion/Exclusion criteria**

*Inclusion criteria*

1. Age: ≥5 years old
2. Sex: males and females
3. Residency: Resident of Nongyang village in Menghai county, Yunnan province, People’s Republic of China
4. Registration, participation: Signing of written informed consent sheet (5-17 year olds: additional written approval by parents or legal guardians), willingness to comply with study procedures (stool submission, drug treatment, alcohol abstinence at day of treatment)
5. Absence of systemic or chronic diagnosed or perceivable illness as assessed by medical personnel upon enrolment and again at each day of treatment
6. Females: not pregnant (as verbally assessed by female medical personnel upon enrolment and again at each day of treatment)

*Exclusion criteria*

1. Age: <5 years
2. Residency: No permanent resident of Nongyang village in Menghai county, Yunnan province, People’s Republic of China
3. Registration, participation: No written informed consent sheet signed or parental approval not obtained, unwillingness to comply with all study procedures
4. Presence or suspicion of any abnormal medical condition which is known or suspected to interfere with anthelminthic treatment
5. Known hypersensitivity to any anthelminthic drugs
6. Recent history of anthelminthic treatment
7. Current or past (within 1 month) participation in any other medical trial
8. For females: Suspected or verified pregnancy

**Treatment and study procedures**

*Location*

Nongyang village in Menghai county, Xishuangbanna prefecture, Yunnan province, People’s Republic of China (Steinmann et al., 2008a; Steinmann et al., 2007).

*Time*

Preparation: August 2008-October 2008

Fieldwork, laboratory diagnosis: November 2008-February 2009

Data analysis and publication: March 2009-June 2009

*Information, enrolment*

The village authorities of Nongyang village will be informed about the study in detail by the study team. Subsequently, the resident population of Nongyang village will be briefed about the study by the village authorities. Upon initiation of the field work, teams of fieldworkers (composed of local health personnel and study team members) will visit all households in the village individually, provide detailed information about the planned study, answer arising questions exhaustively and obtain written informed consent to participate in the study from interested individuals and their legal guardians, if applicable (Appendix 1). Demographic data of participating individuals will also be collected (Appendix 2), and each participant will be assigned a unique identification number in ascending format (Format: XX-YY with X=family number and Y=individual number, starting with 01-01)

*Sample collection and diagnostic procedures for baseline parasitological survey*

Labeled stool sample collection containers will be handed out to interested participants upon signing the informed consent sheet. Participants will be invited to submit two large stool samples over consecutive days or within one week. Filled containers will be collected each morning between 6 a.m. and 9 a.m., and transferred to the laboratory at the Menghai county Center for Disease Control and Prevention.

All stool samples will processed within 6 h of collection. Two Kato-Katz thick smears will be prepared from each sample, and ~1 g of stool weighted and conserved in sodium acetate-acetic acid-formalin (SAF) solution for later analysis by the FLOTAC method. The Kato-Katz thick smear slides will be read within 45 min after preparation, and the SAF-conserved FLOTAC samples will be read within 12 weeks of collection. While the focus of the study is on common STHs (*A. lumbricoides*, hookworm, *T. trichiura*), additional helminths will be diagnosed whenever possible (*Taenia* spp. is known to be common in this community (Steinmann et al., 2008a)).

The total number of available diagnostic results will thus be: two Kato-Katz thick smears/sample, one FLOTAC apparatus with two different solutions/sample (total: three diagnostic test results/sample; six diagnostic test results at baseline). Kato-Katz thick smear slides and the FLOTAC are both read quantitatively.

*Randomization and drug dosage*

All participants with complete diagnostic results will be listed in ascending order according to their identification number, and the four different treatment options coded 1-4. A random sequence of 1s, 2s, 3s and 4s will then be generated, and aligned with the list of participants, thus assigning each individual a specific drug-dosage combination.

The drug dosage will be:

Daily albendazole dose: 400 mg (1 day or 3 days)

Daily mebendazole dose: 500 mg (1 day or 3 days)

For each participant, an identical envelope labeled with his/her name and containing the appropriate drugs according to the assigned treatment will be prepared.

*Treatment procedures, drug dosage and application*

Upon completion of the baseline parasitological survey, all participants with complete diagnostic results and ≥1 STH infection will be invited for treatment. They will be informed again about the treatment procedures, asked not to drink alcohol on treatment days, and to disclose their health and pregnancy status prior to treatment. On the days of treatment, teams of local health personnel and study team members will visit the participants individually in their houses after dinner time, enquire about their health and pregnancy status, and distribute the allocated drugs together with bottled water. Drug intake will be directly observed. This procedure will be repeated two times for those participants allocated to triple-dose treatment.

*Safety assessment:* All participants will be interviewed regarding adverse events of the treatment 24 h after drug application using a detailed semi-quantitative questionnaire providing a grading system for reported symptoms (Appendix 3). A medical doctor will be permanently available to the participants for 24 h after drug application for immediate attention to any adverse drug-related events which will be described in detail on an individual basis.

*Sample collection and diagnostic procedures for follow-up parasitological survey*

Two to three weeks post-treatment, labeled stool sample collection containers will be handed out to the treated study participants again. Participants will be invited to submit again two large stool samples over consecutive days or within one week. Filled containers will be collected each morning between 6 a.m. and 9 a.m., and transferred to the laboratory in the Menghai county Center for Disease Control and Prevention.

All stool samples will processed within 6 h of collection. Two Kato-Katz thick smears will be prepared from each sample, and ~1 g of stool weighted and conserved in SAF solution for later analysis by the FLOTAC method. The Kato-Katz thick smear slides will be read within 45 min after preparation, and the SAF-conserved FLOTAC samples will be read within 12 weeks of collection. While the focus of the study is on common STHs (*A. lumbricoides*, hookworm, *T. trichiura*), additional helminths will be diagnosed whenever possible (*Taenia* spp. is known to be common in this community (Steinmann et al., 2008a)).

The total number of available diagnostic results will thus be: Two Kato-Katz thick smears/sample, 1 FLOTAC apparatus with 2 different solutions/sample (total: 3 diagnostic test results/sample; 6 diagnostic test results at follow-up). Kato-Katz thick smear slides and the FLOTAC are both read quantitatively.

*End-of-study treatment*

At the completion of the follow-up parasitological survey, standard anthelminthic treatment (400 mg albendazole, single dose) will be offered to all participants still harboring STHs, to study participants not eligible for treatment within the study, and to all interested inhabitants of Nongyang village provided they are not pregnant, not suffering from systemic, chronic or specific illnesses preventing anthelminthic treatment, and do not take alcohol or other drugs known to interfere with benzimidazole drugs. Drugs for the treatment of additional helminth infections will be provided to individuals with a diagnosed infection.

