**Sample size**

At least 370 individuals aged ≥5 years will be enrolled. Enrolment will be stopped once 400 individuals have signed up, even if additional volunteers are available. The calculated sample size is based on the following assumptions: A total of 176 individuals (44 in each of the four treatment arms) will be needed to demonstrate that single-dose albendazole is performing better than single-dose mebendazole for the cure of hookworm infections with 90% power using a 1-sided statistical test with an α-level of 0.05. The cure rates of albendazole and mebendazole are assumed to be 75% (76.4% in a recent meta-analysis of all published randomized placebo-controlled trials) and 45% (22.9%, multiplied by 2 to increase safety margin) (Keiser and Utzinger, 2008). To further increase the safety margin, the local prevalence of triple *A. lumbricoides*, *T. trichiura* and hookworm infections is assumed to be 60% (it was 76% during the study in 2006 (Steinmann et al., 2008a)), and the compliance is estimated to be 80%.

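### Drug codes are allocated to everyone with complete stool results, before the infection criterion is applied, so the number of hookworm-positive participants per arm is left to chance: a minor flaw with a free remedy

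*Protocol*

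**What the plan says.** Under Randomization and drug dosage, the protocol defines the list: "All participants with complete diagnostic results will be listed in ascending order according to their identification number". It continues: "A random sequence of 1s, 2s, 3s and 4s will then be generated, and aligned with the list of participants". Each listed person thereby receives a treatment code, and an envelope is prepared for each. No blocking, stratification or equal-number rule is stated.

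The next subsection, Treatment procedures, drug dosage and application, adds the infection condition: "all participants with complete diagnostic results and ≥1 STH infection will be invited for treatment". The End-of-study treatment paragraph confirms that some study participants will not be eligible for treatment within the study.

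Under Sample size: "A total of 176 individuals (44 in each of the four treatment arms) will be needed". The comparison to be powered is that "single-dose albendazole is performing better than single-dose mebendazole for the cure of hookworm infections". Enrolment of 370 to 400 is then justified by two discounts: "the local prevalence of triple *A. lumbricoides*, *T. trichiura* and hookworm infections is assumed to be 60" per cent, and compliance of 80%.

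**The concern.** A person can be listed only once the diagnostic results are complete, so infection status is available when the list is drawn up. Allocating people who will not be treated therefore serves no stated purpose, and the arms that can be analysed for cure become random subsets of the arms as allocated.

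The sample size section names a number per arm, and at the enrolment floor it leaves almost no reserve above that number. If the hookworm-positive participants fall unevenly, one of the two arms in the powered comparison can miss its target even when the total is adequate. That imbalance could be avoided with information already in hand.

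**Working it through.** **1. The protocol's own figures.** Inputs from the Sample size section: cure rates 0.75 and 0.45, one-sided α 0.05, power 0.90. With p̄ = 0.60,

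n = [1.645·√(2·0.60·0.40) + 1.282·√(0.75·0.25 + 0.45·0.55)]² / 0.30² = (1.140 + 0.845)² / 0.09 ≈ 43.8, so 44 per arm.

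Power at 44 per arm is 0.901. Inflation: 176 / (0.60 × 0.80) = 366.7, rounded up in the protocol to 370. Both figures reproduce.

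**2. Numbers available at the planning values.**
- 370 enrolled: 370 × 0.80 = 296 listed; 296 × 0.60 ≈ 178; 178/4 ≈ 44.4 per arm.
- 400 enrolled: 320 listed; 192; 48 per arm.

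The 60% is the prevalence of triple infection. Every triple-infected person has hookworm, so 178 and 192 are lower bounds on the hookworm-positive number at that assumption.

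**3. Spread of one arm, 178 people, 296 listed.**
- Unrestricted sequence: SD = √(178·0.25·0.75) ≈ 5.8; 95% range 33 to 56.
- Equal numbers of each code over the whole list: SD = 5.8·√((296 − 178)/295) ≈ 3.7; 95% range 37 to 52.

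**4. Probability that both single-dose arms reach 44** (simulation, 200,000 to 400,000 draws; multinomial for the unrestricted sequence; for the balanced list, the lower or higher value depends on whether the infected total is held fixed or allowed to vary):

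| Enrolled | Prevalence | Hookworm-positive | Unrestricted | Balanced over whole list |
|---|---|---|---|---|
| 370 | 60% | 178 | 27% | 32–35% |
| 400 | 60% | 192 | 57% | 72–77% |
| 370 | 76% | 225 | 96% | about 100% |
| 400 | 76% | 243 | 99% | about 100% |

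At 370 enrolled and an unrestricted sequence, intermediate prevalences give 57% (at 65%) and 82% (at 70%).

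**5. Effect on power, 370 enrolled, 60% prevalence.**
- Unrestricted: mean 0.900, 95% range across allocations about 0.85 to 0.93.
- Balanced over the whole list: mean 0.902, range 0.875 to 0.925.
- Equal arms among the 178: about 0.904.

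The mean loss is therefore at most about 0.5 percentage point.

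**6. Which part of the remedy does the work.** Given 178 hookworm-positive people and an unrestricted sequence, arm sizes have the same multinomial distribution whether or not uninfected people are on the list. Shortening the list alone leaves the 27% unchanged. Equal numbers among the hookworm-positive give 45/45/44/44 at 370 enrolled and 48 per arm at 400, provided that the 20% loss has already occurred.

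**7. If all the loss comes after allocation.** 370 × 0.60 = 222, so 55 or 56 per arm, each retained with probability 0.80. P(both arms keep at least 44) = P(Bin(55, 0.8) ≥ 44)² = 0.34, or 0.46 with 56 in both. At 400 enrolled, 60 per arm gives 0.85. The unrestricted sequence gives about 0.27 at 370 in this case too.

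**The case against.** The strongest reply is that little is lost. Forty-four is a hard threshold set beside an expected 44.4, so small deviations count as failures although power barely moves. The planning values are also cautious: the mebendazole cure rate was doubled from 22.9% to 45%, and prevalence was cut from 76% to 60%. All of this stands, and it limits the point to a minor one.

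Several stronger readings are tempting, but the documents do not support them.

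- *That listing uninfected people causes the 27%.* It does not. That figure comes from assuming an unrestricted sequence, and the protocol does not say whether the sequence is restricted. With a balanced sequence, listing everyone still leaves 32–35% at 370.
- *That the comparison is biased.* Infection is measured before treatment and is independent of the allocated arm, so leaving out uninfected people does not distort the comparison.
- *That the primary outcome has no valid denominator.* The Data analysis section compares species-specific cure rates, which can be computed only in people with that species. This would remain so for any list defined by infection with at least one STH.
- *That the inclusion criteria are defective for lacking an infection criterion.* They govern enrolment, before any stool is examined. Enrolment, listing and treatment are successive stages, and the enrolment figure already allows for people who are not triple-infected.
- *That the remedy guarantees 44 per arm.* The Sample size section does not say when the 20% is lost. Treatment visits, health and pregnancy re-checks and the follow-up stools all come after allocation.

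**Conclusion.** The point holds as a free improvement of minor severity. The allocation leaves the size of the two powered arms to chance when the information needed to control it is already available, and the allocated set does not match the set to be treated. The cost is balance and a little efficiency: occasional allocations with power near 0.85 instead of 0.90 in the planning case, and practically nothing at the 2006 prevalence.

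The figures assume four equally likely arms, the protocol's 60% and 80%, the normal-approximation test without continuity correction, and, except in step 7, that non-compliance removes people before the list is made. The 27% describes the protocol's planning floor and is not a forecast.

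**What to change.** - Under Randomization and drug dosage, restrict the list to participants with complete diagnostic results and at least one STH infection. Split it into hookworm-positive and hookworm-negative strata, and within each use a blocked sequence with equal numbers of the four codes. Both parts are needed: the shorter list makes the allocated and treatable sets agree, and the restricted sequence within strata controls arm size.
- State infection with at least one STH as a condition for randomisation, not for enrolment.
- Under Sample size, say that the 44 per arm are hookworm-positive participants, and say at which stage the 20% non-compliance is expected, because the target is met by design only if the loss precedes randomisation.

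The cost is a few sentences. The stool results exist when the list is made, and no extra participants, visits or tests are needed.
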